# The efficacy of ball blankets on insomnia in depression in outpatient clinics: study protocol for a randomized crossover multicentre trial

**DOI:** 10.1186/s13063-020-04638-y

**Published:** 2020-08-17

**Keywords:** Insomnia, Depressive disorder, Outpatients, Weighted blankets, Actigraphy, Crossover studies

## Abstract

**Background:**

Depression affects approx. 4% of the global population and is often accompanied by insomnia. Medications used to treat insomnia can have side effects such as development of tolerance and addiction. The Protac Ball Blanket™ (PBB) is a non-pharmacological supplement to sedatives and hypnotics, but evidence for the efficacy of PBB is needed before the treatment is implemented. The objective of this trial is to test the efficacy of PBB on insomnia caused by depression in a randomized controlled design.

**Methods:**

This study is a multicentre, randomized crossover trial with planned inclusion of 45 patients. The randomization procedure is permuted-block randomization with varying block sizes. Patients are allocated into either a sequence “AB” or “BA” each lasting 4 weeks (28 nights). Patients randomized to the “AB” sequence receive treatment A (Protac Ball Blanket™) in the first 2 weeks and switch to treatment B (treatment as usual) in the second period, whereas patients who are randomized to the BA sequence receive treatment B in the first period and treatment A in the second period. The participants will serve as their own control in this design. The primary outcome is changes in total sleep time. Secondary outcome measures are changes in sleep onset latency, number of awakenings, wake after sleep onset, and use of sedatives and hypnotics. Furthermore, quality of sleep, insomnia severity status, and self-reported symptoms of depression, anxiety, interpersonal sensitivity, and neurasthenia will be measured. A paired, two-sided *t* test to compare the means of the differences in the outcomes will be performed.

**Discussion:**

This clinical trial will assess the effect of PBB on depression-related insomnia. The outcomes are of high interest as the PBB is a potential non-pharmacological supplement to medical treatment of patients with insomnia due to depression.

**Trial registration:**

ClinicalTrials.gov Identifier: NCT03730974. Registered on 5 November 2018.

## Background

Depression affects approximately 4% of the global population and is associated with significant morbidity and mortality. Evidence-based treatment of the condition is therefore an important clinical and public health issue [1, 2]. Unfortunately, some symptoms of depression are difficult to manage such as for instance insomnia. Insomnia occurs in the majority of patients with depression [2] and is characterized as problems with initiating sleep, several wake ups, early morning awakening, reduced total sleep time, and daytime dysfunction [3–5], all causing poor sleep quality. The relationship between insomnia and depression is complex. Whether insomnia is part of depression or a separate entity is still debated [6–8]. Insomnia in this trial is addressed as a diagnostic symptom of depression [9]. Possible reasons for insomnia in depression are anxiety, impaired stress regulation, substance abuse, poor sleep hygiene, or ruminations [4, 10]. In both inpatient and outpatient psychiatry, medicine is often used to treat insomnia, but pharmacological treatment has side effects and, importantly, in case of benzodiazepines, there is a risk of drug tolerance and addiction [11] as well as somnolence during day-time. Increased attention on investigating the known and unknown benefits of non-pharmacological treatment options for insomnia due to depression is therefore highly relevant. Non-pharmacological treatments include cognitive behavioural therapy, which has proven effects on insomnia [12–14]. Cognitive behavioural therapy for insomnia (CBT-I) typically includes sleep restriction, stimulus control, cognitive therapy, sleep hygiene, and relaxation training [12–14]. Unfortunately, sleep restriction with formal cognitive restructuring to target hyperarousal, dysfunctional behaviours, and maladaptive beliefs, thoughts, and attitudes is limited to patients without severe cognitive problems who are mentally able to participate in therapy sessions [14, 15]. Participation may therefore be problematic for a number of patients with depression, due to decreased energy and difficulties concentrating and remembering, and in some cases psychotic symptoms. Therefore, additional non-pharmacological treatment options are needed.

The Protac Ball Blanket™ is an option that can be used in all patients including patients with severe cognitive deficits due to depression. It has been shown to decrease sleep disturbances in children with ADHD [16]. Further, it has been used in adult psychiatric inpatient settings in Denmark since the early 1990s for patients suffering from depression, anxiety, agitation, manic episodes, and psychosis. From a clinical perspective, the blanket has been found to enhance the patient’s awareness of the body and its physical delimitation which relieves restlessness, stress, and anxiety and provides a sense of security and calm in mind and body, which for some resolves in improved sleep quality. The theory underlying the reasons for using the PBB for calming purposes is based on theories of Sensory Integration [16–18]. It is hypothesized that the deep pressure stimulation and the sensory inputs from the weight of the blanket are providing sensory input to the Proprioceptive System located in our muscles and joints. This provides us with a sense of body awareness and the movement of the loose plastic balls in the blanket which provide sensory input to the Tactile System reduces the body’s physiological level of arousal and stress, which might improve sleep. Clinical experiences support the use of PBB in depression, but to our knowledge, there are no studies on the exact effects of the blanket and the appropriateness of using PBB in insomnia among adults with depression. Two published dissertations on sleeping problems due to dementia or sense of touch and sense of movement issues in children indicate calming effects of using ball blankets [18, 19]. Overlap in symptoms between these conditions and depression, i.e., anxiety and sleep disturbances, suggest an effect in depression. Currently, ball blankets are used as a non-evidence-based treatment option among adults with depression. However, lack of evidence limits the use in the adult population or may expose some to a useless treatment. Further, if ball blankets are beneficial for a proportion of patients with depression, the lack of data on adult patients hampers further development and improvement of the PBB for the benefit of patients.

An important goal in the treatment of depression is to increase the total sleep time, minimize the sleep onset latency, and improve quality of sleep, and at the same time minimize the use of sedatives [1, 8, 20]. We hypothesize that PBB will extend sleep durations, minimize the sleep onset latency, reduce the number of awakenings, reduce wake after sleep onset, reduce the need for sedatives, improve the quality of sleep, and reduce the self-reported symptoms in patients with insomnia due to depression.

## Methods/design

### Objectives

The objective is to investigate the efficacy of PBB on insomnia caused by depression in a randomized controlled design.

### Hypotheses

The use of PBB on patients with insomnia due to depression will
Primary goal
Extend the total night-time sleep andSecondary goals
2.Reduce sleep onset latency3.Reduce the number of awakenings4.Reduce wake after sleep onset5.Reduce the need for sedatives6.Improve the quality of sleep7.Reduce the self-reported symptoms of patients with depression

### Trial design and study setting

This multicentre trial has a randomized 2-sequence, 2-period, 2-treatment crossover design. The rationale for choosing a crossover design is as follows:
Traditionally, the recruitment of depressed patients for research trials is heavily challenged due to the nature of depression, and by choosing a crossover design, we can achieve the same precision as a parallel group trial with a lower sample size [21].We further expect easier recruitment and fewer drop-outs as all patients get to try the PBB intervention compared to a parallel group design.

We are not including a washout period in the trial design for one reason:
The clinical nature and mechanism of the PBB is unlikely to have a residual effect that persists into the subsequent period, as PBBs only cause effect when patients are exposed to the product.

The data collection period lasts 4 weeks (28 nights in total) with planned inclusion of 45 patients. The study protocol adheres to the SPIRIT (Standard Protocol Items: Recommendations for Interventional Trials) reporting guidelines [22].

The trial takes place in two outpatient settings, The Mood Disorders Clinic, Aarhus University Hospital Psychiatry, Central Denmark Region, and in the Mental Health Department Odense – University Clinic, Mental Health Service, Region of Southern Denmark. Both hospitals are public university hospitals. In Denmark, public hospitals containing outpatient clinics are free of charge and treat all patients in need of urgent treatment of depression.

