#### Secondary outcome measures

Changes in sleep onset latency (SOL) will be measured by actigraphy [time frame: 28 days]. The investigators will measure patients’ sleep onset latency in minutes (time between registered bedtime in sleep diaries and first sleep onset measured by actigraphy) and compare the means of the difference for each participant between the two periods (A and B).Changes in number of awakenings measured by actigraphy [time frame: 4 weeks = 28 days]. The investigators will measure the number of awakenings between first sleep onset and the last wake up time registry and compare the means of the difference between periods (A and B) for each participant.Changes in wake after sleep onset (WASO) will be measured by actigraphy [time frame: 4 weeks = 28 days]. The investigators will measure patients’ total time awake between initial sleep onset and the final morning awakening (WASO) in minutes and compare the means of the difference between periods for each participant.Daily use of sedatives and hypnotics will be measured by medication registration use in sleep diaries [time frame: 4 weeks = 28 days]. The investigators will measure the change in total use of per need sedatives and hypnotics in mg by comparing the means of the difference for each participant between periods.Quality of sleep measured by questionnaire using the Pittsburgh Sleep Quality Index (PSQI) [time frame: data will be collected at baseline (visit 2), after 2 weeks (visit 3), and after 4 weeks (visit 4)]. The investigators will measure and report the change in quality of sleep between period A and B. For each participant, the difference between the PSQI measured at the first and the last visit (2 weeks apart) of the exposure period will be subtracted from the difference between the PSQI measured at the first and the last visit (2 weeks apart) of the control period. The total Pittsburgh Sleep Quality Index Score between 0 and 21, with “0” indicating no difficulty and “21” indicating severe difficulties, is reported. Because there will be less than 30 days between assessment at visit 3 and visit 4 and the standard PSQI is a retrospective 30-day instrument, we will use a modified version of the PSQI in which the patients will only be asked about their subjective sleep quality during the past 14 days.Symptoms of depression will be measured by the self-reported Hamilton Depression Rating Scale (HAM-D_6_). Data will be collected at baseline, after 2 weeks, and after 4 weeks. The investigators will measure the change in self-reported symptoms of depression between periods. For each patient, the difference between the scores measured at the first and last visit (2 weeks apart) of the exposure sequence will be subtracted from the difference between the scores measured at the first and last visit (2 weeks apart) of the control period. The total sum scores between 0 and 50 will be reported, where higher values represent worse outcome.Insomnia Severity Status will be measured by questionnaire using the Insomnia Severity Index (ISI). Data will be collected at baseline, after 2 weeks, and after 4 weeks. The investigators will measure the change in patients’ insomnia severity status between periods. For each patient, the difference between the scores measured at the first and last visit (2 weeks apart) of the exposure period will be subtracted from the difference between the scores measured at the first and last visit (2 weeks apart) of the control period. The total scores between 0 and 28 will be reported, where higher values represent worse outcomes.Patients self-reported symptoms of depression measured by questionnaire using the Major Depression Inventory (MDI) [time frame: data will be collected at baseline (visit 2), after 2 weeks (visit 3), and after 4 weeks (visit 4)]. The investigators will measure the change in self-reported symptoms of depression between periods. For each patient, the difference between the scores measured at the first and last visit (2 weeks apart) of the exposure period will be subtracted from the difference between the scores measured at the first and last visit (2 weeks apart) of the control period. The total score between 0 and 50 is reported, where higher values represent worse outcomes.Symptoms of anxiety will be measured by questionnaire using the Beck Anxiety Index (BAI). Data will be collected at baseline (visit 2), after 2 weeks (visit 3), and after 4 weeks (visit 4).The investigators will measure the change in self-reported symptoms of anxiety between periods. For each patient, the difference between the scores measured at the first and last visit (2 weeks apart) of the exposure period will be subtracted from the difference between the scores measured at the first and last visit (2 weeks apart) of the control period. The total score between 0 and 63 for each visit is reported, where higher values represent worse outcomes.Patient-reported outcomes concerning interpersonal sensitivity, neurasthenia, anxiety, and depression will be measured by questionnaire using The Self-Reported Symptom State Scale (SCL-28) [time frame: data will be collected at baseline (visit 2), after 2 weeks (visit 3), and after 4 weeks (visit 4)]. The investigators will measure the change in self-reported symptoms between period A and B or B and A. For each patient, the difference between the scores measured at the first and last visit (2 weeks apart) of the exposure period will be subtracted from the difference between the scores measured at the first and last visit (2 weeks apart) of the control period. Sub scales are combined to compute a total score. The range for each sub scale is: Interpersonal Sensitivity 0–32, Neurasthenia 0–28, Anxiety 0–32, and Depression 0–24. Both total score and sub scale scores will be reported. The total score ranges between 0 and 112, where higher value represents worse outcomes. Because of an overlap in one question between the sub scales anxiety and depression question, number 31 is only considered in the total sum scores.

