### Statistical methods

Paired, two-sided analyses will be performed. If the differences in the measures between the exposure and control periods for each patient are normally distributed, as we expect, we will use a Student’s *t* test to test the null hypotheses of no differences. For the non-normal distributions, non-parametric tests, e.g. Wilcoxon signed-rank tests or Fisher’s exact tests will be used.

All data with or without protocol violation will be included in the analysis with complete outcome data for all randomized participants. Because the analyses are based on the differences between period A and B or B and A for each patient, we will perform complete case analysis (i.e. participants with missing actigraphic data from one of the periods will be removed from the analysis). An intention to treat analysis will be performed, i.e. patients that in one or both of the periods use an “incorrect”, non-study blanket will be kept in the analyses in their randomized sequence group. We will not account for missing data by imputation.

The level of statistical significance will be set to 5%.

The randomization will determine whether the participants will begin or end with a PBB. The baseline characteristics of these two groups will be presented in a table. Baseline information on sleep will be based on The Pittsburgh Sleep Quality Index (PSQI) and the Insomnia Severity Index (ISI) and not collected via actigraphy.

There will be no wash-out period in this trial because the PBB are expected to have no residual effect persisting in the subsequent periods. This assumption is based on the biological mechanisms of the ball blanket and on clinical experience, but there are no studies to corroborate this expectation. This aspect of the design, however, is expected to lead to bias toward the null, i.e. that the study will not overestimate a potential effect of PBB. The assumption of no carry-over effect in the data will be ruled out in a preliminary test. The sum of the TST values will be calculated for the time period when using PBB and when using patients’ own duvets for each participant. This will be compared across the sequence groups by means of an independent *t* test. If this test yields a statistically significant result, the usual test for differences between the effects of treatment A or B will not be applied [31].

Data will be analysed using Stata IC15 (Stata Corp, College Station, TX, USA).

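### The exposure-only reason for having no washout is not argued for the symptom scales, and the assurance that the effect will not be overestimated fails for their change-score contrast, which estimates 1.0 to 1.5 times the true effect

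*Protocol article*

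**What the plan says.** Under Trial design and study setting, the protocol article introduces its case with "We are not including a washout period in the trial design for one reason". The reason is that the blanket "is unlikely to have a residual effect that persists into the subsequent period", "as PBBs only cause effect when patients are exposed to the product".

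Goal 7 under Hypotheses is "Reduce the self-reported symptoms of patients with depression". Secondary outcome measures serves it with HAM-D6, MDI, BAI and SCL-28, each scored at baseline (visit 2), week 2 (visit 3) and week 4 (visit 4). For anxiety, for example, "The investigators will measure the change in self-reported symptoms of anxiety between periods". For every scale the contrast is the change across the exposure period set against the change across the control period.

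Statistical methods returns to the washout. It says "This assumption is based on the biological mechanisms of the ball blanket and on clinical experience, but there are no studies to corroborate this expectation", and that the design is "expected to lead to bias toward the null, i.e. that the study will not overestimate a potential effect of PBB". The carry-over check is then defined on one outcome: "The sum of the TST values will be calculated for the time period when using PBB" and for the own-duvet period, and the sum is compared between the sequence groups. A significant result cancels the usual treatment test. No check is named for the scales.

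**The concern.** An effect confined to the hours under the blanket is a reasonable premise for actigraphy recorded during those hours. Depression, anxiety, interpersonal sensitivity and neurasthenia are rated at visits and describe how the patient has been. They can change only if better nights affect waking life. The premise therefore does not by itself show that nothing persists on these scales, and no other passage argues it for them.

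The plan's fallback is that carry-over would only make the estimate conservative. That fits a comparison of period means, such as TST. The scales are analysed differently: in sequence AB the duvet period starts from a score already improved by the blanket. If the benefit fades, the fading is counted as worsening under the duvet and added to the blanket's effect. At stake is the size of the reported symptom benefit, which depends on a persistence that the plan neither estimates nor reports.

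**Working it through.** **The plan's own figure.** Sample size uses an SD of the paired difference of 42 min, a target of 20 min, two-sided alpha 0.05 and power 0.80. The non-central t gives power 0.805 at N = 37, and 37 is the smallest N reaching 0.80. The stated figure reproduces. It concerns TST only.

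**Expected scale scores.** Let t be the reduction in score at the end of a blanket period and L the share of it still present at visit 4 in AB. L is not in the documents; the range 0 to 1 is taken. With no period effect, the reductions from visit 2 are:

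| Sequence | Visit 3 | Visit 4 |
|---|---|---|
| AB | t | Lt |
| BA | 0 | t |

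**Planned contrast (blanket-period change minus control-period change).**
- AB: t - (Lt - t) = (2 - L)t
- BA: t - 0 = t
- Mean over equal sequences: (1.5 - L/2)t

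| L | AB | BA | Mean |
|---|---|---|---|
| 0 | 2t | t | 1.5t |
| 0.5 | 1.5t | t | 1.25t |
| 1 | t | t | 1.0t |

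The overstatement is largest, 50%, at L = 0, which is exactly what the plan assumes. An additive period effect enters the two sequences with opposite signs and cancels when they are equal in size. If t = 0, the mean is 0, so the problem is the size of the estimate and not a false-positive rate.

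**Period 1 comparison.** Visit 3 in AB minus visit 3 in BA, adjusted for visit 2, has expectation t - 0 = t for every L, because visit 3 comes before any carry-over.

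**Precision.** Assumed: 37 completers (19 AB, 18 BA), unit SD, equal correlation r between visits, t = 0.5 SD.
- Planned contrast: each patient's value is plus or minus (2 x visit 3 - visit 2 - visit 4), with variance 6(1 - r). At r = 0.6 this is 2.4, so SE = sqrt(2.4/37), about 0.25 SD.
- Period 1 ANCOVA: SE = sqrt(1 - r²) x sqrt(1/19 + 1/18). At r = 0.6 this is 0.8 x 0.329, about 0.26 SD.

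Power from the non-central t (36 and 34 degrees of freedom):

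| r | Planned contrast, L = 0 / 0.5 / 1 | Period 1 ANCOVA, any L |
|---|---|---|
| 0.4 | 65% / 50% / 34% | 36% |
| 0.6 | 82% / 67% / 48% | about 45% |
| 0.8 | 98% / 92% / 77% | 69% |

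**Would the TST pre-test help if extended to the scales?** For TST, the SD of the two-period sum is 42 x sqrt((1 + r)/(1 - r)): 57 min at r = 0.3 and 126 min at r = 0.8. With 37 to 45 patients, power to detect a 10-min difference in sums (half the 20-min target) is about 6% to 9%. Such a test cannot rule carry-over out.

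**The case against.** The strongest reply is that the design section and goal 7 are compatible. A reader might infer that they contradict each other, so that goal 7 can be met only if the washout argument is false. The documents do not support that. The design section denies persistence into the following two-week period, not from night into day. A benefit that lasts through the day and fades within two weeks of withdrawal satisfies both. This stands: it is a tension, not a contradiction.

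A reader might also infer that the plan offers no argument at all for these outcomes. Statistical methods does offer clinical experience and a bias-toward-the-null argument for the whole design. The first is uncorroborated by the article's own admission. The second does not fit the change-score contrast.

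A third tempting inference is that a persisting benefit is credited to the duvet and shrunk below its true size. That holds for a comparison of end-of-period scores, which would estimate t(1 - L/2), with power of 91%, 70% and 38% at L = 0, 0.5 and 1 (r = 0.6). The article does not specify that comparison for these scales. Under its own contrast, full persistence gives the duvet period a change of zero, and the expected estimate is never below t.

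It is also fair that these are secondary outcomes and that supportive analyses are often left to an analysis plan. But the contrast, the conservative-bias statement and the TST-only check are all fixed in the article, and the first two do not fit together.

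**Conclusion.** The point holds in limited form. The no-washout rationale is unsupported, though not refuted, for HAM-D6, MDI, BAI and SCL-28, and the one carry-over check does not cover them. The assurance against overestimation is wrong for these scales: the planned contrast estimates between 1.0t and 1.5t according to an unknown L, and overstates most when there is no carry-over. The multiplier assumes sequences of about equal size, an additive period effect and L between 0 and 1. The power and SE figures also rest on an assumed correlation, an assumed effect of 0.5 SD and 37 completers. The test of no effect is not invalidated, and the primary TST comparison is outside this point.

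**What to change.** 1. In Trial design and study setting and in Statistical methods, limit the no-residual-effect and bias-toward-the-null statements to the actigraphy outcomes.
2. For HAM-D6, MDI, BAI and SCL-28, prespecify the visit 3 score compared between AB and BA, adjusted for the visit 2 score. Report it with its 95% CI beside the crossover estimate, regardless of any pre-test.
3. Do not extend the TST pre-test to the scales, and do not make the reading of a null crossover result depend on the period 1 estimate, which is itself imprecise.

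The cost is a wording change and one ANCOVA per scale, with no new data. The downside is modest power: about 45% at 0.5 SD, correlation 0.6 and 37 completers, below that of the planned contrast at every L shown. Part of the planned contrast's advantage comes from its inflated target; the SEs are close, about 0.26 against 0.25 SD.
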